#### Formative process evaluation

The process evaluation will be guided by the RE-AIM framework [25], which consists of five elements that are known to improve the adoption and implementation of evidence-based health interventions. These five elements include: reach (number, proportion, and extent of participation), efficacy (impact of the guidelines on the teachers, parents, and children), adoption (organizational support for the guidelines), implementation (delivery and use of the guidelines), and maintenance (long-term awareness and use of the guidelines). Table 2 summarizes the application of the RE-AIM framework in this study alongside the planned methodology.

**Table 2 Tab2:** Process evaluation based on the RE-AIM framework [25] and using a mixed-methods approach

ELEMENT	METHOD	INDICATORS	EVALUATION QUESTIONS
Reach	Participation audit	Participation in educational meetings	What proportion of the target participants attended the educational meetings? How many educational meetings were conducted in each participating ECEC?
	Online metrics	Volume and frequency of activities on the online platforms	How frequent did the participants visit the online platforms (website, Facebook)? What are the materials that the participants viewed, interacted with, or downloaded (e.g. brochures, posters, videoclips)? How frequent did the participants leave comments on the available materials? Describe the comments and feedback left by participants on the online platforms.
Efficacy	Online survey	Participants’ perceptions and knowledge	How satisfied were the participants with the dissemination activities and materials? To what extent did parents and teachers know and understand the guidelines for (1) physical activity, (2) sedentary behavior, and (3) sleep?
	Focus group discussion	Supportive strategies enacted and reported by teachers and parents	Describe the strategies that teachers and parents implemented to support children in meeting the guidelines.
Adoption	Focus group discussion	Supportive strategies reported by ECEC administrators/principals	Describe the strategies that ECECs implemented to support the teachers and parents to apply their knowledge to promote healthy movement behaviors.
Implementation	Online survey	Participants’ perceptions	To what extent did the participants find the information and materials to be practicable, accessible, and useful?
	Focus group discussion	Factors related to delivery of activities and information Factors related to implementation of activities by participants	What were the factors that influenced the delivery of information? What were the factors in the school, home, community, social context, or other situational issues that influenced the children in meeting the guidelines (barriers and enablers)?
Maintenance	Online survey	Participants’ knowledge Behaviors of children as reported by teachers and parents	To what extent did parents and teachers know and understand the movement guidelines? To what extent did children in participating ECECs meet the guidelines?

A mixed-methods triangulation design – convergence model with equal weight drawn from the quantitative and qualitative components (i.e., QUAN + QUAL) will be used to gather and analyze data [26]. In this design, quantitative and qualitative data collection methods will be conducted concurrently at each data collection time point, analyzed separately, and converged upon interpretation. This design has been recommended as a means to achieving well-substantiated conclusions on the implementation process. Moreover, a mixed-methods approach to evaluation using the RE-AIM framework has been known to facilitate understanding of complex situations and the factors that lead to implementation outcomes [27]. Quantitative data will be gathered through participation audit, online metrics, and close-ended questions in online surveys. Qualitative data will be gathered through open-ended questions in online surveys and focus group discussions (FGDs).

Participation audit will consist of monitoring the number of educational meetings in each ECEC and the participants’ attendance in the said educational meetings. Online metrics will include the recording of interactions with media that are made available through the social media platforms (i.e., number of hits, likes, shares or downloads of materials), including comments that are left by participants on the available media. Online surveys will be administered at two time points: 3 months (Time 1, T1) and 6 months into the implementation (Time 2, T2).

The online surveys will assess teachers’ and parents’ satisfaction with the educational meetings, perceptions of the usefulness of materials, and knowledge and understanding of the movement guidelines. For the formative component, responses to the online survey will inform the project team so that actions to mitigate barriers and enhance facilitators can be initiated. Based on questions used in previous studies that examined the dissemination of physical activity guidelines [28–30], the online survey questions will include dichotomous questions (i.e., Yes/No), five-point Likert-type scales, and open-ended questions to assess participants’ knowledge and awareness of the movement guidelines.

FGDs will be conducted at T1 and T2 with a subsample of participants (i.e. teachers and principals, *n* = 3 per ECEC, total *n* = 24; parents or primary caregivers, *n* = 3 per ECEC, total *n* = 24) to query the strategies that teachers and parents implemented to enable children to meet the guidelines, and the strategies that ECEC principals implemented to support the teachers and parents. The target sample sizes for the FGDs exceed the recommended sample size for FGDs in projects of this current scale [31]. The discussions will also explore the factors that influenced the dissemination of information, and the factors that challenged and enabled the children meeting the guidelines [32, 33].

#### Summative outcome evaluation

A non-randomized observational study design will be used for the outcome evaluation, where outcomes will be compared between the implementation group and the comparison group. The implementation group will consist of teachers and parents from the ECECs that participated in the dissemination activities; the comparison group will consist of teachers and parents from a matched group of ECECs who have yet to join the implementation. ECECs in the comparison group will join educational meetings and receive all materials in the subsequent school year after the implementation period. The primary outcome of interest is the extent to which children in the ECEC groups meet the guidelines for physical activity, sedentary screen time, and sleep. The secondary outcomes are the knowledge and awareness of healthy movement guidelines by teachers and parents.

Teachers and parents will be invited to respond to online surveys at two additional time points: immediately following the implementation period (Time 3, T3), and 4 months post-implementation (Time 4, T4). These surveys will measure the secondary outcome by assessing the participants’ knowledge and awareness of the movement guidelines. The surveys for parents will include additional questions to measure the primary outcome by assessing the extent to which children meet the guidelines through a parent-proxy questionnaire. The said proxy-report questionnaire is made up of items from validated English-language questionnaires [34, 35] which were translated and back-translated [36] for use among parents of young children in Hong Kong. The translated questionnaire had been found to have good internal consistency (Cronbach’s alpha = 0.762), and is currently being used in an ongoing longitudinal study of child development in Hong Kong. Finally, open-ended questions will query on family strategies that relate to children meeting the movement guidelines.

For a further measure of the primary outcome, parents will also be invited to let their children wear accelerometers for objective measurement of physical activity, sedentary behavior, and sleep. The Actigraph GT3X (Actigraph, Pensacola, FL, USA) will be used, which is an accelerometer equipped with antero-posterior, vertical, and medio-lateral axes [37]. The GT3X is a widely used device for physical activity and sedentary behavior monitoring, and cut-points have been validated for young children [38]. Evidence-based accelerometer data collection for children will be followed [39]. Accelerometer epoch length will be set at 15 s, and each child will be asked to wear the GT3X above the right hip on a waist belt during waking hours for seven consecutive days. The parents/caregivers will also be instructed to remove the GT3X during water-based activities (e.g., bathing, swimming), and to record the time when the GT3X was put on and removed (i.e., record the wear/non-wear time in a diary).

The data gathering procedures for the process and outcome evaluations are summarized in Table 3, according to the timeline of measurements.

**Table 3 Tab3:** Timeline of data gathering procedures for the process and outcome evaluations

	Time 1	Time 2	Time 3	Time 4
Participation audit	•	•		
Online metrics	•	•		
Online survey (knowledge and awareness of movement guidelines)	•	•	•	•
Focus group discussions	•	•		
Online survey (parent-proxy questionnaire on primary outcome)			•	•
Accelerometer monitoring			•	

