#### Recruitment

Eight ECECs, from across the three major districts of Hong Kong (i.e., Hong Kong Island, Kowloon, New Territories), will be recruited to join the implementation. The inclusion criteria for ECECs are that they: (1) are included in the published list of kindergartens by the Education Bureau, (2) follow the *Kindergarten Education Curriculum Guide of Hong Kong* [23], and (3) offer classes across three kindergarten levels (i.e., K1, K2, K3). A second group of eight ECECs, who meet the same eligibility criteria and with comparable background to the first group (i.e., ECEC size, location), will also be recruited to join a comparison group for the outcome evaluation. This second group will participate in the activities for the dissemination of the movement guidelines (i.e., educational meetings, social media, resource materials) in the school year following the implementation period. Given the constraints associated with the recruitment of ECECs to participate in projects during a pandemic, the recruitment process will be purposive. The timeline for joining the project will be the prerogative of each ECEC (i.e., hence, the group to which they will be allocated to).

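### The comparison ECECs are called matched, but comparability in size and location is only a recruitment aim, each ECEC's joining year sets its group, and no estimable form of the primary model adjusts for those factors

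*Protocol article*

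**What the plan says.** All places are in the protocol article.

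- **Summative outcome evaluation:** the design is non-randomised and observational, and "the comparison group will consist of teachers and parents from a matched group of ECECs who have yet to join the implementation".
- **Recruitment, implementation group:** "Eight ECECs, from across the three major districts of Hong Kong" are recruited.
- **Recruitment, comparison group:** "A second group of eight ECECs" is sought, "who meet the same eligibility criteria and with comparable background to the first group (i.e., ECEC size, location"). The same section says "the recruitment process will be purposive" and "The timeline for joining the project will be the prerogative of each ECEC (i.e., hence, the group to which they will be allocated to").
- **Data processing and analysis:** the primary logistic regression has three kinds of term: group, child characteristics and ECEC. The secondary comparisons account for participant characteristics and ECEC. Neither ECEC size nor district is named, and the text does not say whether ECEC is a fixed or a random term.
- **Table 3:** the parent-proxy measure of the primary outcome is taken at T3 and T4 and the accelerometer measure at T3. Both time points follow the implementation period.
- **Potential challenges and mitigations:** the lack of randomisation is named as a possible limitation.

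**The concern.** The word matched tells a reader that the investigators arranged the two sets of eight ECECs to agree on stated factors. The Recruitment section describes something weaker: an aim of comparable size and location, with group membership following from each ECEC's own timing. No ratio, tolerance or procedure is given by which the aim would be met.

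If the groups do end up differing in district or size, the analysis has to deal with it. The model terms named do not do so in any form that also yields a group effect. With 8 against 8 ECECs, moving a few centres changes the mix noticeably. With no outcome measured before implementation, a difference that existed beforehand cannot be seen in the outcome data or removed from them.

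**Working it through.** **1. The two descriptions side by side.** The Summative outcome evaluation asserts a matched group. The Recruitment section gives the aim (comparable size and location), the method (purposive) and the rule that sets the group (the ECEC's chosen year). The aim gives partial control, since the investigators can choose which later-joining ECECs to approach. It is not an enforced match, because they do not decide which ECECs join early or late.

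**2. What the ECEC term can do.** There are 16 ECECs, 8 nested in each group. Take the design matrix with ECEC as fixed indicators. Size is coded as one term and district as two; these codes are illustrative, as the article gives none.

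| Terms | Columns | Rank |
|---|---|---|
| Intercept + ECEC | 16 | 16 |
| + group | 17 | 16 |
| + group + size + district | 20 | 16 |
| Intercept + group + size + district, no fixed ECEC | 5 | 5 |

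- *Fixed ECEC:* the indicators already span size and district, but they span group as well. Adding group does not raise the rank, so no separate group effect can be estimated.
- *Random or cluster ECEC:* group is estimable. The ECEC term then describes variation between centres or corrects the standard error, and a difference in size or district mix between the groups stays in the group coefficient.

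Either way, there is no estimable group effect adjusted for size and district.

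**3. How large the distortion could be (assumed rates).** The article gives no outcome rates by district and no district counts. Suppose one district has 25% of children meeting a guideline component and the others 40%. The odds are 0.333 and 0.667, so the district has half the odds. Suppose it holds 1 of 8 implementation and 4 of 8 comparison ECECs, with equal numbers of children per ECEC and no true effect.

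- Implementation: 0.125 × 0.25 + 0.875 × 0.40 = 0.381
- Comparison: 0.5 × 0.25 + 0.5 × 0.40 = 0.325
- Odds ratio: (0.381/0.619) / (0.325/0.675) = 0.616/0.481 = 1.28

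On the log scale this is ln 1.28 / ln 1.5 = 0.61 of the odds ratio of 1.5 assumed in Participants and sample size. With the imbalance reversed, the null would appear as 1/1.28 = 0.78.

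The same calculation for size, also on assumed values:

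| Large ECECs, implementation v comparison | Size odds ratio 1.25 | 1.5 | 2.0 |
|---|---|---|---|
| 5 of 8 v 3 of 8 | 1.06 | 1.11 | 1.19 |
| 6 of 8 v 2 of 8 | 1.12 | 1.22 | 1.41 |

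**4. Cost of adjusting.** Between-ECEC degrees of freedom fall from 16 − 2 = 14 to 16 − 5 = 11. The two-sided 5% critical t goes from 2.145 to 2.201, a ratio of 1.026.

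If group and district are correlated, the standard error also rises. In the 1 of 8 against 4 of 8 example the correlation is (1×4 − 7×4)/√(8×8×5×11) = −0.40. The variance inflation is 1/(1 − 0.164) = 1.20, so the standard error is about 9% larger. Together, 1.026 × 1.093 = 1.12, or about 12% wider in that example (a linear approximation with one district indicator).

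**The case against.** The strongest reply has four parts.

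**The design does control size and location in part.** A matched group need not mean matched pairs. Purposive recruitment to a comparable size and location is a form of group-level matching, and an ECEC can choose its year while the investigators choose which later joiners to accept. This stands. A reader might infer that imbalance is not prevented at all, or that matching is impossible here; the Recruitment section does not support either. What it supports is that balance is sought and not assured.

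**ECEC is in the model, and size and district are attributes of an ECEC.** This is right for fixed ECEC terms, so a flat statement that the factors are not adjusted for would be wrong. It does not rescue the analysis, because the same terms remove the group effect.

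**Chance of imbalance.** A reader might want a probability. If all 12,870 splits of 16 ECECs into 8 and 8 were equally likely, and the districts held 5, 5 and 6, a difference of at least three ECECs in some district would occur in 46% of splits, but a difference of at least four in only 14.5%. The article gives no district counts, and its comparability aim makes equally likely splits the wrong model. These figures are a random-split benchmark under assumed counts and do not estimate the risk in this study.

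**Disclosure and condensation.** The article is open about purposive recruitment and the lack of randomisation, and a full covariate list is often left to a longer plan. That is fair as to detail. However, the article itself makes the matching claim, names the two factors and lists the model terms, and these do not fit together.

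It is also true that self-chosen timing may bring differences in motivation or readiness, which neither matching nor adjustment on size and district would remove.

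**Conclusion.** The point holds in a limited form. The word matched claims more than the Recruitment section provides, and the primary model as named gives no estimable group effect adjusted for the two factors the plan itself picks out. Table 3 offers no pre-implementation outcome as a safeguard.

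The structural part rests only on ECEC being nested in group and needs no assumed figures. The size of any bias does rest on assumptions: odds ratios of 1.06 to 1.41 under no effect in the size examples and 1.28 in the district example, none of them backed by rates in the article. They show that a plausible imbalance could matter beside a planned odds ratio of 1.5, not that one exists. The change is worth making in a non-randomised comparison of 8 against 8 centres because it is cheap.

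**What to change.** 1. In Summative outcome evaluation, replace the word matched with: recruited to be comparable in size and location, with group determined by each ECEC's choice of joining year. If a matching procedure was in fact used, state it instead.
2. In Data processing and analysis, for the primary and the secondary outcomes, specify ECEC as a random or cluster term and add district and ECEC size as ECEC-level covariates. The first part is essential: beside fixed ECEC indicators, the two covariates change nothing.
3. Report the distribution of district and size by group for the 16 ECECs.

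The cost is a wording change and about three ECEC-level terms, whose values should be known from recruitment. Intervals widen by about 2.6% through the loss of three degrees of freedom, with further widening where group and district are correlated (about 12% in all in the example above). With only 16 ECECs there is little room for further centre-level covariates.

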#### Participants and sample size

In the formative evaluation, participants will consist of teachers (*n* = 24), administrators/ principals (*n* = 8), and parents/primary caregivers of children aged 3 to 6 years (*n* = 240) from the first group of eight ECECs (i.e., the implementation group).

In the outcome evaluation, the required sample size was calculated for the planned logistic regression analysis of the primary outcome (see Data Processing and Analysis section). It was calculated that assuming an effect size of adjusted odds ratio = 1.5, alpha at 0.05, and power at 80%, a total sample size of *N* = 242 parents/primary caregivers (and their children) is required from the two groups of ECECs (i.e., the implementation and comparison groups). With an assumed 40% non-response rate from the combined implementation and comparison groups (*N* = 480 parents) and a further 10% with incomplete data, we expect complete responses from a sample size of *N* = 240.

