The secondary outcome of knowledge and awareness of the movement guidelines by parents and teachers will be compared between the implementation and comparison groups using descriptive and inferential statistics, whilst accounting for participant characteristics (e.g., age, sex) and ECEC. Parametric statistics will be used when assumptions of normality are met. All statistical analysis procedures will be performed on SPSS 26.0 with statistical significance set at *p* < 0.05.

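### As the plan reads, only the implementation group answers the knowledge survey before T3, so any effect of being surveyed cannot be separated from the dissemination effect on the secondary outcome

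*Protocol article*

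**What the plan says.** All references are to the protocol article.

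- **Who is in the formative evaluation.** Participants and sample size draws its teachers, principals and 240 parents "from the first group of eight ECECs (i.e., the implementation group").
- **When and what the formative surveys ask.** Under Formative process evaluation: "Online surveys will be administered at two time points: 3 months (Time 1, T1) and 6 months into the implementation (Time 2, T2"). They cover satisfaction with the meetings, "perceptions of the usefulness of materials, and knowledge and understanding of the movement guidelines", and the question formats are chosen "to assess participants’ knowledge and awareness of the movement guidelines".
- **What the comparison group is for.** Recruitment says that a second set of eight ECECs "will also be recruited to join a comparison group for the outcome evaluation".
- **When the outcome is measured.** Under Summative outcome evaluation, teachers and parents "will be invited to respond to online surveys at two additional time points", namely T3 and T4. "These surveys will measure the secondary outcome by assessing" what participants know about the guidelines.
- **Schedule.** Table 3 has a single row for the knowledge and awareness survey, marked at all four times and not divided by group.
- **Analysis.** Under Data processing and analysis, knowledge and awareness "will be compared between the implementation and comparison groups using descriptive and inferential statistics", with allowance for participant characteristics and ECEC. Earlier survey exposure is not mentioned.

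**The concern.** Being asked about a guideline can lead a teacher or parent to look it up, discuss it or remember it. The formative work reported in the Dissemination plan found that participants broadly knew guidelines existed but knew little of the specific minutes and hours. That is the kind of fact a questionnaire can prompt someone to check. If only one group has been asked before T3, the between-group difference contains both what dissemination achieved and what the questioning achieved.

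Knowledge and awareness are the only outcomes named for the adults, and the third stated aim is the impact of dissemination on parents, teachers and children. A survey effect would also be absent from a later roll-out without evaluation surveys. The problem lies in who is surveyed and when, which the protocol fixes. It is not a detail that an analysis plan could supply afterwards.

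**Working it through.** The plan states no figure on this point, so there is nothing to reproduce.

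**Step 1. Prior knowledge surveys, counted from the sections above.**

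| Before | Implementation | Comparison | Gap |
|---|---|---|---|
| T3 | 2 (T1, T2) | 0 | 2 |
| T4 | 3 (T1, T2, T3) | 1 (T3) | 2 |

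**Step 2. Can the analysis separate the two effects?** Write the expected group difference as δ + τ, with δ the effect of dissemination and τ the effect of two extra surveys. Being offered the T1 and T2 surveys coincides exactly with group. Age, sex and ECEC do not vary along that line, so adjusting for them leaves τ in place. Table 3 has no survey before implementation that could help.

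**Step 3. What would τ have to be to matter?** τ is an assumption throughout. Inputs:
- n = 120 parents per group: half of the 240 complete responses expected in Participants and sample size, equal split assumed.
- Two-sided α = 0.05 (the protocol gives 0.05 but not the sidedness), δ = 0, responses treated as independent.
- Base awareness p of 15% (physical activity) and 79% (screen time) from the Background; 50% is an assumed middle value.

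With q = p + τ and m = (p + q)/2:
- se0 = √(2m(1−m)/n)
- se1 = √([p(1−p) + q(1−q)]/n)
- chance of a significant result = Φ((τ − 1.96·se0)/se1) + Φ((−τ − 1.96·se0)/se1)

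Example, p = 0.15 and τ = 0.05: m = 0.175, se0 = 0.0491, se1 = 0.0489. The first term is Φ(−0.94) = 0.173 and the second 0.001, giving 17%.

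| Base | τ = 2 points | 5 points | 10 points | 15 points |
|---|---|---|---|---|
| 15% | 7% | 17% | 49% | 80% |
| 50% | 6% | 12% | 34% | 65% |
| 79% | 7% | 17% | 56% | 93% |

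For a continuous knowledge score, assumed effects of 0.1, 0.2 and 0.3 SD give 12%, 34% and 64%. The nominal rate is 5%. On the odds-ratio scale, 15% against 20% is (0.20/0.80)/(0.15/0.85) = 1.42, and 15% against 25% is 1.89. These odds ratios only restate the assumed 5 and 10 points.

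**Step 4. With equal histories** (2 against 2 before T3, 3 against 3 before T4), a survey effect common to both groups cancels and the rate returns to 5%.

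**The case against.** The strongest reply is that much of this is inferred and none of it is measured.

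- **Comparison group at T1 and T2.** Table 3 does not divide by group, so its absence is a reading of the text. The reading is strong: T1 and T2 are defined inside an evaluation limited to implementation ECECs, and those surveys ask about meetings the comparison group has not yet had.
- **Same questions, same parents.** A reader might infer that identical items are repeated to the very parents compared at T3. The protocol does not say that items repeat unchanged. The overlap of parents is suggested only by 240 being half of the 480 approached, and no split of the 480 is given.
- **Size.** Nobody is said to be told the correct answers. The implementation group also receives meetings, updates at least every two weeks and materials on the same content for eight months, and two surveys may add little to that. This stands, and it limits what can be claimed.
- **Focus groups.** It is tempting to count them as further testing. They ask about strategies, barriers and enablers, not knowledge, so they add little to the argument.
- **Surveys as part of the programme.** T1 and T2 answers do inform the project team's actions. But Table 1 lists only meetings, social media and resource materials, and the comparison group's later programme is defined by those three.
- **Harm from the remedy.** Surveying comparison parents might change behaviour before the primary outcome is measured at T3. The implementation group already has that exposure, so equalising it removes an imbalance there too.

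The discussion of limitations does name the lack of randomisation. That is a separate matter: randomising ECECs would not cure unequal survey histories.

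**Conclusion.** The asymmetry holds as the plan reads: two more prior knowledge surveys in the implementation group at both T3 and T4, with no planned analysis able to separate their effect from dissemination. The direction probably favours the implementation group. The size is unknown. The illustrative false-positive rates run from barely above nominal at 2 points to serious at 10 points or more, and they rest on an assumed survey effect, 120 completers per group, independence and no dissemination effect.

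A reader might go further and conclude that the knowledge result will be mostly a testing artefact, or that the primary outcome is affected in the same way. The protocol supports neither. It contains no figure for a survey effect, and Table 3 schedules the parent-proxy questionnaire only at T3 and T4, so that instrument has no unequal repeat use. The point is confined to the secondary outcome and is worth correcting because the correction is cheap.

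**What to change.** **Preferred.** Send comparison-group teachers and parents the same short online knowledge items at T1 and T2, without the satisfaction and usefulness items. Both groups then have the same survey history. The cost is two short mailings to ECECs already being recruited and some added awareness, which is then common to both groups.

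**If that is not possible, or those waves have passed** (implementation began in September 2021, which puts T1 at about December 2021 and T2 at about March 2022):
- In any remaining formative wave, give knowledge items to a random half of implementation parents only.
- Keep the full T3 and T4 comparison as the main analysis. Report the less-tested half against the comparison group as a sensitivity analysis. With 60 against 120 parents (equal split assumed) the standard error grows by √[(1/60 + 1/120)/(1/120 + 1/120)] = √(0.0250/0.0167) = 1.22, about 22%. Teachers are not covered.
- State in the report that the knowledge difference includes any effect of repeated surveying.

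Repeating the parent comparison without focus-group participants is a minor optional check.
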